## **7. Statistical considerations**

### **7.1 Power and Sample Size Calculation**

The calculation is based on the primary outcome, time to first epinephrine dose. Prior data report a median of approximately 165 seconds (IQR of 139 to 173 seconds). Using the Greco et al. approach, and using the 1st and 3rd quartiles, we estimate SD as  $(173-139)/1.35 = 25.2$  seconds. With a two-sided

$\alpha=.05$  and 90% power to detect a clinically meaningful absolute reduction of 35 seconds, and assuming similar variability between groups, 18 teams (9 per arm) are required.

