## 7.2 Group Allocation

Randomization will be conducted in a 1:1 ratio at the level of the team and stratified by study site using an online random number generator. Randomization will be conducted in blocks of two to ensure equal distribution of teams across study arms. Study packages will be prepared with opaque envelopes to achieve allocation concealment. Sequentially numbered recruitment packages provided for each site will contain unique identifier codes for participants, along with study arm assignments. Personnel who enroll participants and those who assign participants to interventions will have no advance access to the sequence. On the trial day, the principal investigators or delegated investigators will obtain written informed consent from participants before any study procedures, and selection criteria will be checked prior to participation in the study. Immediately after written consent, the authorized staff will access only the assignment function to obtain the participant's allocation. Assignment will occur once per participant, with audit trails documenting day and time.

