#### 423 **7.4.2 Primary Outcome - Time to administer 1st dose of epinephrine**

424 Due to the small sample size, non-parametric approaches will be used to account for potential violations  
425 of assumptions underlying parametric tests. Boxplots will be generated to assess the distribution of data  
426 in both study arms. If the data are approximately symmetric and normally distributed, the mean  
427 difference will be estimated; if the data are skewed or non-normally distributed, the median difference  
428 will be estimated instead. Bootstrapping with 10,000 resamples will be used to calculate 95% confidence  
429 intervals for the estimated differences. Permutation tests with 10,000 iterations will be conducted to  
430 determine 2-sided p-values.

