#### 431 **7.4.3 Secondary Outcomes – Time to other critical tasks during cardiac arrest management**

432 These outcomes include time to initiate CPR, time to first dose of defibrillation, time to establish  
433 advanced airway, time to 1st and 2nd drugs to treat hyperkalemia, chest compression fraction and peri-  
434 shock durations. Time to these critical tasks and BLS outcomes (e.g., chest compression fraction, peri-  
435 shock pause durations) will be analyzed using the same non-parametric approaches applied to the  
436 primary outcomes. After assessing the data distribution, bootstrapping and permutation tests with 10,000

iterations will be used to estimate 95% confidence intervals and p-values for the differences. A template table is presented below.

| Variables | InterFACE-AR
(n = 9) | PALS cards
(n = 9) | Median/mean
Difference
(95% CI)* | P
value** |
|-----------|-------------------------|-----------------------|----------------------------------------|--------------|
| Outcome 1 | X (X – X)               | X (X – X)             | X (X, X)                               | X            |
| Outcome 2 | X (X – X)               | X (X – X)             | X (X, X)                               | X            |
| ...       | X (X – X)               | X (X – X)             | X (X, X)                               | X            |

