#### **7.4.6 Secondary outcomes - UEQ and TAM (for intervention group only)**

The User Experience Questionnaire (UEQ) and the Technology Acceptance Model (TAM) survey will be administered to participants in the InterFACE-AR group only. Rather than presenting data for each individual item, we will report the statistical summaries (mean and standard deviation) for each construct within both tools. The UEQ includes six constructs: attractiveness, perspicuity, efficiency, dependability, stimulation, and novelty. The TAM includes two constructs: perceived usefulness and perceived ease of use. For each construct, the mean and standard deviation will be reported, and Cronbach's alpha will be calculated to assess the internal consistency of the items within each construct.

In the case of missing data, a complete case analysis will be conducted. No multiple imputations are planned. All statistical tests will be two-sided with a type one error risk of 5%. All statistical analyses will be performed with R software (version 4.5.0; Foundation for Statistical Computing).

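### Randomisation is stratified by site, but the permutation test and bootstrap do not mention site; read literally, the test is valid but loses power if the two hospitals differ

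*Combined protocol and SAP*

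**What the plan says.** Section 7.2 allocates 1:1 "at the level of the team and stratified by study site", in blocks of two. Section 2.4 names the sites as the children's hospitals in Geneva and Calgary. How the teams divide between them is not stated.

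For the primary outcome, section 7.4.2 estimates a mean difference, or a median difference if the data are skewed. It takes a bootstrap interval from 10,000 resamples and adds: "Permutation tests with 10,000 iterations will be conducted to" obtain two-sided p-values. Section 7.4.3 carries "bootstrapping and permutation tests with 10,000" iterations over to the other task times, chest compression fraction and peri-shock pauses. The mixed models in 7.4.5 have a random intercept for the simulation event and no site term.

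Site, strata and blocks appear nowhere in 7.4. The plan neither restricts the permutation to sites nor says that it will ignore them.

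**The concern.** A permutation test takes its reference distribution from re-drawing the allocation as the trial could have drawn it. Stratification keeps the arms balanced within each hospital, so a difference between hospitals largely cancels out of the treatment contrast. Shuffling over all 18 teams brings in allocations that the design rules out, such as most intervention teams sitting in one hospital. Any site difference then widens the reference distribution without widening the real sampling variation of the contrast. The p-value comes out too large and the true type I error falls below the nominal 5%.

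What is at stake is power. There is little to spare with 9 teams per arm, and site differences are plausible: section 2.5 admits attending physicians, fellows, senior residents and physician assistants from several specialties, and the mix may not be the same in two countries.

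**Working it through.** **Inputs from the plan.** Section 7.1: SD (173 - 139)/1.35 = 25.2 s, effect 35 s, "18 teams (9 per arm) are required". Section 7.4.6: "All statistical tests will be two-sided with a type one error risk of 5"%. Section 7.2: stratification by site, blocks of two.

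**Assumptions.** Site split 10/8 (9/9 also run); normal outcomes; 25.2 s is the SD within a site; a site difference d between 0 and 50 s.

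**Step 1: the plan's own figure.** Section 7.1 claims "90% power to detect a clinically meaningful absolute reduction of 35 seconds". The normal formula gives 2 × [25.2 × (1.960 + 1.282)/35]² = 10.9, so 11 per arm. Nine per arm gives 83.8% power by the normal formula and 79.0% by the t-test. The 90% is not reproduced. That is a separate matter, but it sets the baseline here: about 78-79%.

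**Step 2: how far the reference set differs.** With a 10/8 split:
- all 18 teams shuffled: C(18,9) = 48,620 allocations
- shuffled within site: C(10,5) × C(8,4) = 252 × 70 = 17,640
- shuffled within blocks of two: 2⁹ = 512

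Only 17,640/48,620 = 36% of the unrestricted shuffles are balanced within site.

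**Step 3: expected size.** Pooling the sites adds d² × (10/18)(8/18) = 0.247d² to the variance in the reference distribution. At d = 25.2 s the SD is inflated by √1.247 = 1.117. The effective critical value is 1.96 × 1.117 = 2.19, a two-sided size of about 0.029. At d = 50 s the factor is √1.972 = 1.404, the critical value 2.75 and the size about 0.006.

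**Step 4: simulation (mean difference, 10/8 split, 35 s effect).**

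| Site difference | Size: unrestricted / within site | Power: unrestricted / within site |
|---|---|---|
| 0 s | 0.052 / 0.052 | 78% / 78% |
| 10 s | 0.046 / 0.050 | 78% / 79% |
| 20 s | 0.035 / 0.051 | 75% / 80% |
| 25.2 s (1 SD) | 0.030 / 0.048 | 70% / 78% |
| 35 s | 0.018 / 0.049 | 62% / 78% |
| 50 s | 0.006 / 0.050 | 48% / 79% |

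A separate run at 40 s gives power of about 58% and 79%. The simulated sizes agree with step 3.

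**Step 5: variations (unrestricted / within site).**
- Median difference, 10/8: power 66% / 66% at 0 s, 55% / 61% at 25.2 s, 32% / 53% at 50 s.
- 9/9 split, mean difference: 69% / 77% at 25.2 s, 44% / 71% at 50 s. The within-site figure drops at 50 s because an incomplete block can leave arms 5/4 within a site, and the statistic in this run was not site-adjusted.
- 25.2 s read as the total SD including site: 81% / 89% at 25.2 s.
- Permutation within the blocks of two: size 0.044-0.048, power about 71-73% in this run whatever the site difference.

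**Step 6: the interval.** The plan's unstratified percentile bootstrap covers about 90% at 0 s, 94% at 25.2 s and 98% at 50 s. Its mean width rises from 43 s to 49 s to 63 s. Resampling within site and arm keeps the width near 40 s, but with 4-5 teams per cell it covers only about 88-90% throughout.

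**The case against.** The plan is silent on site; it does not decide to ignore it. A reader might infer that the team chose an unrestricted shuffle, but 7.4.2 states no permutation scheme at all, so the unrestricted test is only the literal reading. This objection stands. It does not remove the need for a sentence, since the two schemes give different p-values from the same data.

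The size of the loss rests on a site difference that the documents do not give, and several features point to a small one: the same manikin and scripted actors at both sites (section 3.2) and a standard camera setup (6.1). A difference of 25 s is a full SD, and 40 s exceeds both the 34 s interquartile range and the 35 s target effect in 7.1. At 10 s the cost is about one point of power. This also stands. Standardising the room does not, however, standardise the staff, and staff mix is the likelier source of a difference.

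Finally, strict fidelity to the design would mean permuting within the blocks of two. With only 512 allocations that has lower power than the unrestricted test when the sites are alike, so within-site permutation is a pragmatic choice and should be described as one.

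**Conclusion.** The point holds as a low-cost improvement. As literally written, the tests in 7.4.2 and 7.4.3 do not use the stratification in 7.2. For the mean difference with a 10/8 split, the cost is nil with no site difference, about 1 point of power at 10 s, about 8 points at 25 s (size about 0.03 against 0.05) and about 20 points at 40 s. For the median the gap at 25 s is about 6 points (55% against 61%). All of this rests on an assumed site difference and an assumed split, so the actual loss is unknown.

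A reader might infer that the mismatch invalidates the primary test or inflates false positives. It does not: the error is towards conservatism and the only harm is conditional loss of power. Nor can the bootstrap interval simply be called conservative. With no site difference it covers about 90%, below its nominal level, because the arms are small.

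**What to change.** In 7.4.2 and 7.4.3:
- Permute arm labels only within site.
- Use a site-weighted average of the within-site arm differences as both test statistic and estimate. This also handles unequal arms within a site. For medians it is a slightly different estimand from the overall median difference, and the SAP should say so.
- Obtain the 95% interval by inverting the within-site permutation test, or use a stratified bootstrap with a small-sample correction. Do not use a plain percentile bootstrap within site and arm.
- State that permutation is within site rather than within the blocks of two, and why.

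In 7.4.5, add site as a fixed effect.

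The cost is a short SAP paragraph and some R code, with test inversion needing a little more than a strata option. No new data are needed, and essentially no power is lost if the sites are alike. The change should be made before the data are unlocked, because choosing the scheme afterwards could be driven by the results.

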#### 431 **7.4.3 Secondary Outcomes – Time to other critical tasks during cardiac arrest management**

432 These outcomes include time to initiate CPR, time to first dose of defibrillation, time to establish  
433 advanced airway, time to 1st and 2nd drugs to treat hyperkalemia, chest compression fraction and peri-  
434 shock durations. Time to these critical tasks and BLS outcomes (e.g., chest compression fraction, peri-  
435 shock pause durations) will be analyzed using the same non-parametric approaches applied to the  
436 primary outcomes. After assessing the data distribution, bootstrapping and permutation tests with 10,000

iterations will be used to estimate 95% confidence intervals and p-values for the differences. A template table is presented below.

| Variables | InterFACE-AR
(n = 9) | PALS cards
(n = 9) | Median/mean
Difference
(95% CI)* | P
value** |
|-----------|-------------------------|-----------------------|----------------------------------------|--------------|
| Outcome 1 | X (X – X)               | X (X – X)             | X (X, X)                               | X            |
| Outcome 2 | X (X – X)               | X (X – X)             | X (X, X)                               | X            |
| ...       | X (X – X)               | X (X – X)             | X (X, X)                               | X            |

#### 7.4.4 Secondary Outcomes – Medication dose deviations

Medication dose deviations are defined as 10% deviated from the guideline dosage. Epinephrine, amiodarone and calcium doses will be examined and measured as dichotomous outcomes. They will be presented as counts and percentages for each study arm. Odds ratios will be calculated to assess the relative effect of the intervention. To address small cell counts, the Haldane–Anscombe correction will be applied. Risk differences (RD) will also be calculated to assess the absolute effect of the intervention, with 95% confidence intervals estimated using Newcombe’s method. Fisher’s exact test will be used to calculate p-values. A template table is presented below.

|                                        | InterFACE-AR | PALS cards | Odds ratio
(95% CI)* | Risk difference
(95% CI)** | P
value*** |
|----------------------------------------|--------------|------------|-------------------------|-------------------------------|---------------|
| Epinephrine dose deviation >10%, n (%) | X (X%)       | X (X%)     | X (X, X)                | X (X, X)                      | X             |
| Amiodarone dose deviation >10%, n (%)  | X (X%)       | X (X%)     | X (X, X)                | X (X, X)                      | X             |
| Calcium dose deviation >10%, n (%)     | X (X%)       | X (X%)     | X (X, X)                | X (X, X)                      | X             |

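### Fisher's exact test on 9 teams per arm is valid but gives up power for the dose-deviation outcomes and can disagree with the Newcombe interval beside it; Boschloo's test is a cheap improvement

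*Combined protocol and SAP*

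**What the plan says.** Section 7.4.4 covers three drugs: "Epinephrine, amiodarone and calcium doses will be examined and measured as dichotomous outcomes". Each template row carries an odds ratio with its interval, a risk difference "with 95% confidence intervals estimated using Newcombe’s method", and a p-value: "Fisher’s exact test will be used to calculate p-values". The closing paragraph of section 7.4.6 sets the level for the whole plan: "All statistical tests will be two-sided with a type one error risk of 5" percent.

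The size comes from section 7.1 ("18 teams (9 per arm) are required") and the unit of randomization from section 7.2 ("Randomization will be conducted in a 1:1 ratio at the level of the team"). Section 7.1 bases its calculation on time to first epinephrine only.

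Four things are not stated for the dose outcomes: the expected deviation rates, the unit of analysis (team or dose), whether the Newcombe interval is continuity-corrected, and which result leads if interval and p-value differ.

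**The concern.** Fisher's test conditions on the total number of deviations. With 9 teams per arm few tables are possible for any given total, so the attainable significance levels are coarse and the real false-positive rate falls well below 5%. The unused part costs power, in a trial with little to spare for yes/no outcomes.

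The Newcombe interval is built differently and is less conservative in its uncorrected form. One row can therefore show an interval that excludes zero next to a p-value above 0.05. With three drugs there are three chances of such a row. Without a rule fixed in advance, the emphasis could be chosen after the data are seen.

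**Working it through.** **Inputs.** Two-sided 5% (section 7.4.6); 9 teams per arm (section 7.1, and the column heads of the section 7.4.3 template); 1:1 allocation by team (section 7.2). Assumption: one yes/no result per team for each drug, none missing. Deviation rates are also assumptions, shown as a range.

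The plan gives no figure for these outcomes that could be reproduced. The 9 per arm is taken as planned. It does not follow from the stated inputs for the primary outcome: 2 × (1.960 + 1.282)² × 25.2² / 35² = 10.9, or 11 per arm. That is a separate matter.

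**Method.** Let a and b be the teams with a deviation in each arm. There are 10 × 10 = 100 possible tables. The type I error at a common rate p is the sum, over the tables a test rejects, of Bin(a; 9, p) × Bin(b; 9, p), and the maximum is taken over p. Power uses p₁ and p₂ in place of p.

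**Step 1: size.**

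| Rule | Tables rejected | Maximum type I error | At p = 10% | At p = 20% |
|---|---|---|---|---|
| Fisher, p ≤ 0.05 | 28 | 2.10% | 0.07% | 0.7% |
| Boschloo, p ≤ 0.05 | 34 | 3.28% | 0.65% | 2.5% |
| Uncorrected Newcombe interval excludes 0 | 38 | 5.70% | 0.7% | 3.5% |

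Boschloo's 34 tables contain all 28 of Fisher's. The six extra are 4/9 v 0/9, 7/9 v 2/9, 9/9 v 5/9 and their mirror images. At p = 0.5 these add (4 × 126 + 2 × 36 × 36) / 2¹⁸ = 3,096 / 262,144 = 1.18%, and 2.10% + 1.18% = 3.28%. Fisher's mid-p rejects in the same 34 tables.

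**Step 2: power, at assumed rates.**

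| Rates | Fisher | Boschloo | Gain (points) | Chance that uncorrected Newcombe excludes 0 but Fisher p > 0.05 |
|---|---|---|---|---|
| 80% v 0% | 98.0% | 99.7% | 1.7 | 1.7% |
| 90% v 10% | 94.2% | 97.2% | 3.0 | 3.6% |
| 40% v 20% | 6.8% | 10.9% | 4.1 | 9.3% |
| 60% v 20% | 27.9% | 35.0% | 7.1 | 15.1% |
| 80% v 20% | 62.5% | 72.1% | 9.6 | 13.6% |
| 50% v 10% | 29.6% | 40.4% | 10.7 | 20.3% |
| 50% v 0% | 50.0% | 74.6% | 24.6 | 24.6% |
| 44% v 0% | 35.5% | 61.5% | 26.0 | 26.0% |

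**Step 3: one contradictory row.** Take 4/9 v 0/9.
- Fisher: 2 × C(9,4) / C(18,4) = 2 × 126 / 3,060 = 0.082.
- Newcombe, uncorrected: the Wilson limits are 0.189 to 0.733 for 4/9 and 0 to 0.299 for 0/9. Lower limit: 0.444 − √[(0.444 − 0.189)² + (0.299 − 0)²] = 0.051. Upper limit: 0.444 + √[(0.733 − 0.444)² + 0²] = 0.733.

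The full list, with mirror images behaving alike:

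| Table | Fisher p | Newcombe 95%, uncorrected |
|---|---|---|
| 7/9 v 2/9 | 0.057 | 0.096 to 0.780 |
| 4/9 v 0/9 and 9/9 v 5/9 | 0.082 | 0.051 to 0.733 |
| 5/9 v 1/9 and 8/9 v 4/9 | 0.131 | 0.010 to 0.716 |

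With the continuity-corrected interval only 7/9 v 2/9 disagrees. In neither version does Fisher reject while the interval includes zero.

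**Step 4: other sizes.** If the unit is not the team, or teams drop out as incomplete cases, Fisher's maximum type I error is 0.6% at 6 v 6, 1.3% at 7 v 7, 2.9% at 18 v 18 and 2.6% at 27 v 27. It is conservative at every size checked.

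**The case against.** A reader might infer that Fisher's test conflicts with the plan's 5% error risk. The documents do not support that. The 5% is a nominal upper limit, and a test that stays at 2.1% meets it. Boschloo's test is also below 5%, and at a 10% common rate it too is under 1%, so part of the shortfall comes from having 18 teams rather than from Fisher's test.

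A reader might also take one figure from the power table as the loss. That is not supported either. The documents give no rate by arm for any of the three drugs; section 1.2 has only a relative reduction in defibrillation dosing errors from an earlier trial. The largest gains need a deviation rate of zero, or nearly so, in one arm.

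Three further objections carry some weight:

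- **Conditioning.** Fisher's test matches the permutation tests used for the time outcomes. Boschloo's 5% control is an average over possible totals. Given exactly four deviations among 18 teams, its chance of rejecting is the 0.082 of step 3. That is a real difference in principle. Unconditionally the limit holds: the maximum stays at 3.28% when the two sites are given different null rates, with the same site split in both arms.
- **Unit.** Section 4 defines medication errors as a count and a frequency, section 7.4.5 expects repeated epinephrine doses, and the 7.4.4 template shows no n. The unit must be settled first, and the fix does so.
- **Multiplicity.** Three drugs are tested with no stated adjustment, so some caution is welcome. But Fisher's conservatism varies with the unknown rates and is no substitute for a stated rule.

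None of this shows a loss of power from using a test whose rejection region contains Fisher's and whose maximum size is 3.3%.

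**Conclusion.** The point holds as a cheap improvement, not as an error in the plan. At 9 v 9 with one result per team, Fisher's test uses at most 2.1 of the 5 percentage points allowed. Boschloo's test uses up to 3.3 and never has less power. The gain is about 0 to 26 points, depending wholly on assumed rates.

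The disagreement between p-value and interval is possible under the plan's own choice of methods. It covers five table patterns if the Newcombe interval is uncorrected and one if it is corrected. The missing rule on which result leads is a gap in either case.

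The weight is minor. These are secondary outcomes with no power claim, and the counts and effect estimates in the table would not change.

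**What to change.** In section 7.4.4:

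1. Replace Fisher's exact test with Boschloo's two-sided unconditional exact test, ordered by Fisher's two-sided p-value. Fisher's mid-p is an equivalent choice at 9 v 9.
2. State that the team is the unit, with one yes/no result per team and drug. Say how several doses of one drug are combined, and how a team that never gives the drug is counted.
3. Name the Newcombe version.
4. State that significance is judged by the p-value and that the interval describes precision.

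If Fisher's test is kept, items 2 to 4 are still needed.

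The cost is a few sentences and an add-on R package, with no new data or participants. The test is less familiar to readers. Disagreement is reduced but not removed. Boschloo's test still differs from the uncorrected Newcombe interval at 5/9 v 1/9 and 8/9 v 4/9 (9.5% chance at 50% v 10%, 8.0% at 60% v 20%). With the corrected interval it differs the other way, rejecting at 4/9 v 0/9 and 9/9 v 5/9 while the interval includes zero. That is why item 4 is needed with either version.
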